# Study protocol of a randomized controlled trial to test the effect of a smartphone application on oral-health behavior and oral hygiene in adolescents with fixed orthodontic appliances

**DOI:** 10.1186/s12903-018-0475-9

**Published:** 2018-02-07

**Keywords:** Study protocol, Behavioral intervention, App, M-health, Prevention, Oral health promotion, Oral health behavior, Oral hygiene

## Abstract

**Background:**

Adolescents with fixed orthodontic appliances are at high risk of developing dental caries. To date, new smartphone technologies have seldom been used to support them in the preventive behavior that can help prevent dental caries. After an intervention-mapping process, we developed a smartphone application (the WhiteTeeth app) for preventing dental caries through improved oral-health behavior and oral hygiene. The app, which is intended to be used at home, will help adolescents with fixed orthodontic appliances perform their oral self-care behavior. The app is based on the Health Action Process Approach (HAPA) theory, and incorporates several behavior-change techniques that target the psychosocial factors of oral-health behavior. This article describes the protocol of a randomized controlled trial (RCT) to evaluate the effects of the WhiteTeeth app on oral-health behavior and oral-hygiene outcomes (presence of dental plaque and gingival bleeding) compared with those of care as usual, in patients aged 12–16 with fixed orthodontic appliances.

**Methods/design:**

The RCT has two conditions: an experimental group that will receive the WhiteTeeth app in addition to care as usual, and a control group that will only receive care as usual. Care as usual will include routine oral-health education and instruction at orthodontic check-ups. In the western part of the Netherlands 146 participants will be recruited from four orthodontic clinics. Data will be collected during three orthodontic check-ups: baseline (T0), 6 weeks of follow-up (T1) and 12 weeks of follow-up (T2). The primary study outcomes are the presence of dental plaque (measured with a modified Silness and Loë Plaque Index); and gingival bleeding (measured with the Bleeding on Marginal Probing Index). Secondary outcomes include changes in self-reported oral-health behaviors and its psychosocial factors identified by the HAPA theory, such as outcome expectancies, intention, action self-efficacy, coping planning and action control.

**Discussion:**

Since the intervention was designed to target psychosocial factors in the motivational and volitional components of the behavior-change process, we hypothesize that the app will cause greater improvements in oral-health behavior and oral hygiene more than traditional oral-health-promotion programs (i.e., care as usual).

**Trial registration.:**

The trial has been registered with the Dutch Trial Register (NTR6206: 20 February 2017).

**Electronic supplementary material:**

The online version of this article (10.1186/s12903-018-0475-9) contains supplementary material, which is available to authorized users.

## Background

In 2011, 60% of young Dutch adults had had orthodontic treatment during adolescence [1]. Despite its functional and esthetic benefits, fixed-appliances therapy is associated with an increased risk of dental caries, mainly in the form of white-spot lesions, whose estimated prevalence ranges from 50 to 90% [2–5]. After orthodontic treatment, the lesions can become an esthetic problem, and may progress to more extended caries lesions [6, 7].

Although fluoride administration (e.g. fluoride mouth rinses) and the regular and effective removal of plaque from all tooth surfaces are essential to preventing oral diseases [8, 9], patients undergoing fixed orthodontic treatment have difficulty reducing dental plaque, as fixed orthodontic appliances (brackets) impede cleaning [10]. Previous studies also showed that only 50% of patients used fluoride mouth rinses as prescribed [11, 12]. Over 60% of orthodontists in the Netherlands stated that patients’ oral hygiene deteriorates during orthodontic treatment [13]. A majority of orthodontists indicated that 5–10% of patients interrupt orthodontic treatment prematurely due to poor oral hygiene [13, 14]. A recent cross-sectional study in the Dutch city of Almere showed that most young orthodontic patients had low levels of oral hygiene and did not follow oral-health recommendations [15]. This emphasizes the need for intervention strategies to improve oral hygiene in young people with such appliances.

Today’s use of smartphones offers new opportunities for developing oral-health interventions. This high use – particularly by young people – could ensure comprehensive access to adolescents with fixed orthodontic appliances [16–18]. Smartphones may thus be an appropriate medium for providing oral-health care information, changing oral-health behavior and improving oral hygiene.

For this reason, we used the intervention-mapping protocol [19] to develop a smartphone application (the WhiteTeeth app) intended to prevent dental caries by improving adolescents’ oral-health behavior and oral hygiene during fixed orthodontic treatment. As part of the intervention mapping process, we conducted a systematic review with meta-analysis and a cross-sectional study in which we analyzed oral-health behaviors and psychosocial factors (i.e. intervention targets) in adolescents [15, 20]. The results of this suggested that the Health Action Process Approach (HAPA) theory would be an appropriate theory for underpinning the present intervention [21]. Incorporating several behavior-change techniques that target the psychosocial factors identified by the HAPA theory, the WhiteTeeth app thus focuses (1) on controlling dental plaque levels through improved dental cleaning and (2) on increasing the use of fluoride mouth rinse.

In this article we describe the design of a randomized controlled trial (RCT) to compare the effectiveness of the WhiteTeeth app with that of care as usual. The primary objective of the study is to determine whether the use of the WhiteTeeth app by orthodontic patients aged 12 to 16 improves oral-health behavior and oral hygiene. The primary outcomes of this RCT are changes in dental plaque levels, and gingival bleeding upon marginal probing. The secondary outcomes are changes in oral-health behaviors, including tooth-brushing and the use of dental-cleaning aids and fluoride mouth rinse, and psychosocial factors of oral-health behavior. We will test the mediating effects of psychosocial factors on changes in oral-health behaviors and oral hygiene. Our hypothesis is that the use of the WhiteTeeth app in the intervention group will improve oral-health behavior and oral hygiene more than usual care does (the control group). We expect changes in the psychosocial factors to be associated with the factual changes in oral-health behavior.

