### Sample size

The sample-size calculation will be based on the primary outcome measure, the modified Silness and Loë plaque index. Between treatment groups we have assumed a 0.35 difference in mean change at week 12 [38]. The required sample size is 2 × 63 patients (setting α = 5% (two-tailed), a standard deviation (s) of 0.7, and the power (1-β) = 0.80) [39]. Allowing for an expected loss of 15%, a sample of 73 patients is needed in each group.

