### Statistical analysis

All statistical analysis will be based on the intention-to-treat (ITT) principle. The participants’ characteristics will be summarized using descriptive statistics (mean, standard deviation, frequency). Baseline data will be used to investigate the characteristics of any participants who discontinue or deviate from the trial and/or intervention. The magnitude of change over time across study groups will be examined by linear mixed models for continuous primary and secondary outcome variables, controlling for baseline variables and other covariates that may relate to the outcome.

To take account of the correlated observations within the participant, mixed-model analyses will be used. Two analyses will be performed: 1) to evaluate the overall intervention effect, 2) to evaluate the intervention effect at different follow-up times. This will be done by adding time and the interaction between time and intervention group variable into the linear mixed models. For mediation analysis, we will perform linear regressions based on Baron and Kenny’s recommendations [40]. A Sobel test will be used to test the mediating effect. A z-value greater than 1.96 and a *p*-value lower than 0.05 will indicate a significant mediating effect [41].

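### Two primary outcomes are named, but the sample size and its 5% alpha are set for plaque alone, and the article does not reconcile the two

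*Protocol article*

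**What the plan says.** The protocol article describes its primary outcomes in several places, and they do not agree.

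- **Abstract, Methods/design:** "The primary study outcomes are the presence of dental plaque", and the sentence goes on to add gingival bleeding. Two outcomes.
- **Background, last paragraph:** "The primary outcomes of this RCT are changes in dental plaque levels, and gingival bleeding upon marginal probing". The same two outcomes.
- **Bleeding upon marginal probing (BOMP):** the paragraph on inter-rater reliability also speaks of primary outcome measures in the plural.
- **Sample size:** "The sample-size calculation will be based on the primary outcome measure, the modified Silness and Loë plaque index". One outcome. The two-tailed 5%, the power of 0.80, the assumed difference of 0.35 at week 12 and the standard deviation of 0.7 all belong to this calculation. Nothing equivalent is given for bleeding.
- **Statistical analysis:** the outcomes go to "linear mixed models for continuous primary and secondary outcome variables". The section gives no order between the two primary outcomes, no division of alpha, and no statement of whether one or both must succeed. Its only significance threshold is for the mediation test.

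**The concern.** A result in which one primary outcome is significant and the other is not is entirely realistic. With two primary outcomes and a design built for one, the article does not say whether that result is a success. The answer determines the properties of the trial. If one significant outcome is enough, the 5% no longer describes the risk of a false primary claim. If both are needed, the 80% no longer describes the chance of success. The second primary outcome also has no planned power under any rule.

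**Working it through.** **Inputs from the Sample size section:** difference 0.35, standard deviation 0.7 (standardised effect 0.35/0.7 = 0.5), two-sided α = 0.05, power 0.80, 63 evaluable patients per group, 15% loss, 73 recruited per group.

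**Inputs not in the article (assumed):** the correlation r between the plaque and bleeding test statistics, and the standardised effect on bleeding. Ranges are shown for r; for bleeding, the plaque value of 0.5 is used.

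**Step 1. Reproduce the stated size.**
n per group = 2 × (1.96 + 0.8416)² / 0.5² = 2 × 7.849 / 0.25 = 62.8, rounded up to 63. This matches. The 73 follows from 63 × 1.15 = 72.45, rounded up. So the stated size is that of a single outcome tested at the full 5%.

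**Step 2. Either outcome counts, each at two-sided 5%.**
Chance of at least one false positive = 1 − P(|Z₁| < 1.96 and |Z₂| < 1.96), with Z₁ and Z₂ bivariate normal with correlation r. For r = 0 this is 1 − 0.95² = 0.0975.

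| Assumed r | At least one false positive |
|---|---|
| 0 | 9.75% |
| 0.3 | 9.5% |
| 0.5 | 9.1% |
| 0.7 | 8.4% |
| 0.8 | 7.8% |
| 0.9 | 7.0% |

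**Step 3. Both outcomes must be significant at 5%.**
The chance of a false claim is at most 5%. For power, the expected test statistic with 63 per group is 0.5 × √(63/2) = 2.806. Power for plaque alone is Φ(2.806 − 1.96) = 0.801. With the same effect on bleeding, power for both is 0.801² = 0.642 at r = 0, then 0.668 at r = 0.3, 0.689 at r = 0.5 and 0.715 at r = 0.7. That is about 64% to 71%.

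**Step 4. Equal split of alpha (2.5% each), for comparison.**
The critical value becomes 2.241, so plaque power with 63 per group is Φ(2.806 − 2.241) = 0.714. Restoring 80% needs 2 × (2.241 + 0.8416)² / 0.25 = 76.0, rounded up to 77 evaluable per group.

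**Step 5. Fixed sequence, plaque then bleeding, each at 5%.**
If there is no true effect on plaque, any false claim requires plaque to be significant first, which has probability at most 5%. If plaque has a true effect, the only possible false claim is on bleeding, again at most 5%. Plaque is still tested at 5%, so its power stays at 80.1% and n stays at 63. A confirmatory claim on bleeding requires both tests to succeed, so under the assumptions of Step 3 its power is the same 64% to 71%.

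**The case against.** The strongest reply is that an order of testing or an either/both rule commonly belongs in the analysis plan. That document is not shown, and a journal article condenses what lies behind it. This is right as far as it goes: the absence of a multiplicity rule would not be a finding alone. It does not dispose of the conflict, because the article is not silent here. It names two primary outcomes in three places and then sizes the trial as if there were one. Even if an analysis plan supplies a rule, the article's statements on the primary outcome still disagree.

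Three stronger readings are tempting, and the article does not support them.

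- **Each primary outcome is tested at 5%.** This is an inference. The 5% is an input to the plaque sample size, and no level is stated for bleeding.
- **The false-positive rate is nearly doubled.** This needs a rule that either outcome suffices, which the article does not state, and weakly correlated tests. Both indices are scored on the buccal side of the same teeth, so positive correlation is plausible and 9.75% is a ceiling. If both must succeed there is no inflation.
- **Six tests are in play, from two outcomes each assessed overall, at 6 weeks and at 12 weeks.** The Statistical analysis section lists overall and by-time analyses but does not say that any of them may be claimed as the primary result, and the Sample size section ties the planned effect to week 12.

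The primary objective's wording, "improves oral-health behavior and oral hygiene", is also out of step with the listing of behavior as a secondary outcome. That is a separate minor point of wording and does not enter these figures.

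It can also be objected that making plaque the sole primary outcome would demote a prespecified one after registration and the start of recruitment. That objection stands, and a fixed sequence avoids the demotion.

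**Conclusion.** The point holds as a conflict within the article: there are two primary outcomes, and a sample size and alpha for one of them. Its consequence depends on a rule that the article does not give. With either outcome sufficing at 5%, the risk of a false primary claim is at most 9.75%, and about 8% to 9.5% if the test statistics correlate at 0.3 to 0.8. With both required, the risk stays within 5% but power is about 64% to 71% instead of 80%, assuming a standardised effect of 0.5 on bleeding and a correlation of 0 to 0.7. The conflict is certain from the text. The sizes are conditional, since the article gives neither the correlation nor an expected effect on bleeding.

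**What to change.** Before unblinding, make two changes.

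1. In the Statistical analysis section or the analysis plan, state a fixed sequence: plaque at week 12 is tested first at two-sided 5%, being the outcome and time point for which the trial was sized, and gingival bleeding at week 12 is tested at 5% only if plaque is significant.
2. In the Sample size section, replace the reference to a single primary outcome measure with a statement that plaque is the first of two primary outcomes and that the 80% power applies to plaque only.

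Both outcomes remain primary. The 63 evaluable and 73 recruited patients per group stand, and the power for plaque is unchanged. The cost is that bleeding cannot be claimed as confirmatory if plaque fails. Because recruitment began in November 2016 and the trial is registered, the change has to be reported as a protocol modification, which the Dissemination plan section already provides for.

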## Methods/design

This study is a multicenter, parallel, randomized controlled trial with two conditions: an experimental group that will receive the WhiteTeeth app in addition to care as usual, and a control group that will receive only care as usual. Data will be collected during three orthodontic check-ups: baseline (T0), 6 weeks of follow up (T1) and 12 weeks of follow up (T2) (Fig. 1).

**Fig. 1 Fig1:**
[figure not shown]
An overview of the study procedures and design

### Participants and recruitment

One hundred forty-six orthodontic patients aged 12 to 16 will be recruited in four orthodontic clinics in the western Netherlands. The study sites will be eligible if (1) standard oral-health instructions are administered according to the clinical guidelines of the department of orthodontics at the Academic Centre for Dentistry Amsterdam (ACTA) (See paragraph ‘Care as usual’); if (2) the clinicians are orthodontists registered in the Dutch orthodontic specialist register, or are postgraduate orthodontic students supervised by a registered orthodontist; if (3) the orthodontists are willing not to change their method of providing oral-health education or instructions during the study period (care as usual); if (4) there is scope for the researcher to inform patients about treatment allocation and the app (in the case of participation in the intervention group); and if a dental chair is available for the oral-health assessments. We will include the same number of participants from each study site.

Before the study starts, a presentation on it will be given at the eligible clinics. Patients who meet the eligibility criteria (Table 1) will be informed about the study by their clinician. They will then receive an information letter and an informed consent form (see Additional file 1), and have two visits before the baseline measurements. The letter will include information on the intervention, the study design, and ethics. Patients will be recruited over a 3-month period. The baseline assessment will be scheduled after patients’ and their parents’ written informed consent has been received.

**Table 1 Tab1:** Eligibility criteria

Patients will be eligible for the study if they meet the following criteria:
- Boys or girls aged 12 to 16.
- For at least 6 weeks, they must have maxillary and mandibular fixed orthodontic appliance therapy, which consists of bonding at least premolar-to-premolar with edgewise appliances and their modifications.
- They have not been scheduled for removal of fixed orthodontic treatment before the end of the study.
- They have no physical and/or mental disabilities that will impede their ability to perform their own oral hygiene activities.
- They are not engaged in other oral-health education or research program.
- They do not have enamel and dentine dysplasia and/or craniofacial malformation (e.g. cleft).
- They have a sufficient command of the Dutch language.
- They possess a smartphone with software IOS ≥7 or Android ≥4.1.
- Patients and their parents are able or willing to give informed consent.
- Patients must not use medication that may affect plaque accumulation, for example antibiotics and antibacterial mouth rinses.

### Randomization

Randomization to the intervention group or control group will be performed at the patient level. A co-author who is not involved in data collection or analysis will use a random sequence generator (http://www.random.org) to allocate patients in a random sequence to the intervention or control group. In a separate room after completion of the baseline measurements, an independent researcher will tell individual participants to which group they have been allocated. If this is the intervention group, the researcher will help them install and unlock the app on their smartphone, and will also provide information on how to use it. To identify dental plaque during the intervention period, participants in the intervention group will receive twelve disclosing tablets (Gum® Red-Cote®). To prevent treatment contamination, adolescents in the control group will not have access to the intervention, as the app will be locked with a personal code that will only be provided to the adolescents in the experimental group.

### Care as usual

Care as usual will be provided according to the orthodontic protocol at the Academic Centre for Dentistry Amsterdam (ACTA). Whether in the intervention group or control group, all patients will receive oral dental-health education and instructions on plaque control at each visit.

Approximately every 6 weeks, orthodontists will invite their patients for a check-up visit, when they will adjust the braces, evaluate dental hygiene and the progress of the teeth, and, if necessary, provide oral-health education. On the basis of the ACTA guidelines, they will recommend the following oral-health behavior to their patients.

First, to control dental plaque levels, patients will be recommended to brush their teeth with fluoride-containing toothpaste at least twice a day according to the 5-step method. Thus, (1) after brushing the gingival sites, they should brush (2) above and then (3) under the bracket on the buccal sites of the teeth. They should end by brushing (4) the occlusal sites and (5) the lingual or palatinal sites of the teeth. These five steps take approximately three minutes to fulfill [11].

Next, to ensure proper plaque removal, the orthodontists will recommend the use of dental aids (e.g. a proxy brush to clean the tooth surfaces around the brackets). To prevent dental caries during orthodontic treatment, they will also highly recommend the daily use of fluoride-containing mouth rinse and toothpaste [9, 11]. Finally, they will recommend patients to limit their consumption of sugars, refined carbohydrates and acid drinks/soft drinks [22].

### The behavioral intervention: WhiteTeeth app

The app is intended for use at home as an add-on intervention to care as usual. The intervention is based on the Health Action Process Approach (HAPA) theory (Fig. 2), which has demonstrated its usefulness to understanding oral hygiene behaviors in adolescents with fixed orthodontic appliances [15, 21]. The theory classifies the establishment of behavior into two phases: a motivational, intention-forming phase, and a volitional phase in which intention is translated into action [21]. The WhiteTeeth app integrates several behavior-change techniques (BCTs) that target these motivational and volitional behavior-change processes [23, 24]. BCTs addressing the factors of the motivational phase include: providing information on health consequences, visualizing dental plaque with disclosing tablets [25], and demonstrating the desired behavior [24]. BCTs addressing factors in the volitional phase include self-monitoring [26], goal-setting and implementation intentions [27, 28], coping planning (via volitional sheets) [29], and behavioral goal reminders [30, 31]. For the experimental group the WhiteTeeth app is available in the App Store for IOS ≥7+ and in the Play Store for Android ≥4.1 as ‘Witgebit’ (free of charge).

**Fig. 2 Fig2:**
[figure not shown]
The Health Action Process Approach Model [21]

Upon installing and opening the WhiteTeeth app, participants in the intervention group will be required to respond to registration questions and to provide some personal details. These questions will cover the frequency of tooth brushing, the use of fluoride mouth rinse and dental cleaning aids, the length of brushing sessions, and the type of toothbrush. The personal details pertain to outcomes that motivate them to maintain good oral health. Adolescents can select from pre-established outcome-expectancies, such as gum health, fresh breath, plaque removal and whitening. Messages can thus be individualized.

In the next part of the registration process, which is intended to help adolescents identify their dental plaque levels, they will be asked to use the disclosing tablets and to take a selfie of their teeth on which dental plaque is visualized by the disclosing tablet. The participant has to fit the selfie into a fixed window, upon which the app will superimpose a grid. The adolescent will then be asked to register the amount of plaque by clicking the disclosed areas in the grid. The app will interpret the number of clicks (i.e. absence or presence of plaque). Then, on the basis of this plaque assessment and of the answers to the questions on oral-health procedures during the registration phase, the app will provide feedback. If the adolescent has complied with the oral-health recommendations and if dental plague is absent, positive reinforcement will be given. If the adolescent has not complied with these recommendations or if dental plaque is present, personal oral-health advice will be given in short videos and a peer model (i.e. an adolescent with fixed orthodontic appliances) will demonstrate how to clean teeth with fixed appliances. Adolescents will then set a particular goal with regard to tooth-brushing frequency and duration, the use of a proxy brush and/or fluoride mouth rinse (goal-setting). Next, they will be required to formulate when and where they will perform the oral-health behavior (formulating “if-then” goals or an implementation intention). As part of the implementation planning, the app will provide an option for setting reminders for oral-health-behavior tasks. The action plans formulated will be saved on the main page of the app. At the end of the installation process, the app will encourage adolescents to use the brushing timer daily and to monitor their oral-health behavior by registering in the app whether they have performed their tasks.

Every day throughout the 12-week intervention period, push-notifications will be sent instructing adolescents to use the app to enter whether or not they have accomplished their daily dental activities, and to remind them to use the brushing timer when brushing their teeth (at installation, adolescents set the time at which they would like to receive this notification). When adolescents decide to brush, they have the option of turning on the timer. As well as showing the time elapsed during brushing, the timer supports good tooth brushing by showing where and how to brush according to the 5-step method. When adolescents have completed brushing, the app provides positive reinforcement.

Each week, adolescents will be asked via the app to evaluate their dental plaque levels and review their behavioral goals. For this purpose, they will use a disclosing tablet to visualize the dental plaque. They will also be asked to take a selfie of the result and to indicate the visualized dental plaque (following the same procedure as in the registration phase). On the basis of the information both on the selfie – which indicates an increase or decrease in the number of clicks and thus the amount of plaque – and on the activities performed that week, the app concludes whether the adolescent’s goals have been attained. It then compliments the adolescent for using the app, and, if necessary, helps him or her to set new goals or to adapt the existing ones. If adolescents have failed to attain their goals, they can formulate coping plans, i.e., “if-then” plans specifying how they can deal with difficult situations. To establish these, they use volitional sheets, i.e., sheets with pre-established difficult situations and solutions, such as “If I’m too tired to brush my teeth in the evening, then I’ll brush my teeth right after dinner.” These coping plans will be saved on the main page of the app, so adolescents will be reminded of them when they open the app.

If the adolescent does not use the app, it will send personalized text-messages every three days reminding them to use it. These messages will be based on information obtained during installation of the app. For example, “Brushing will help to keep your teeth healthy and beautiful.”

For two weeks, a prototype of the app was pre-tested by 28 adolescents with fixed orthodontic appliances. The data from this pilot test showed that the adolescents appreciated the app for its high usability and were very satisfied with it – particularly with the videos.

